## Introduction

Pectus excavatum (PE) is the most common congenital chest wall deformity affecting 0.1%–0.8% of live births, affecting boys more than girls. Operative repair is indicated when symptoms or signs of heart and/or lung dysfunction are present,^1^ or when the patient is much concerned about the cosmetic appearance and psychosocial problems occur.^2 3^ The optimal age for repair is between 12 and 16 years.^4^ Numerous surgical techniques have been developed to correct PE, of which the Nuss procedure is now among the most commonly employed techniques.^5 6^ The Nuss procedure involves inserting a convex steel bar beneath the sternum to reposition the sternum anteriorly and thereby effectively correcting the deformity.^7^ It is associated, however, with substantial postoperative pain, despite the use of epidural analgesia or patient-controlled intravenous opioid administration.^8 9^ Pain management is the critical component of postoperative care as postoperative pain has implications for activity and quality of life^10^ and is the primary factor determining the length of hospital stay.^11^

Therefore, interest is growing in finding new ways to alleviate postoperative pain, such as perioperative music interventions. In previous studies in adult surgical patients, recorded music interventions reduce pain medication consumption and improve the management of pain and anxiety.^12–20^ However, in children and adolescents undergoing surgery, a definite conclusion about the effect of recorded music interventions has yet to be drawn.^21^ Especially in paediatric surgical procedures associated with substantial postoperative pain, such as the Nuss procedure, music interventions might be effective in reducing children’s pain and anxiety. We designed a multicentre randomised controlled trial (Interventions with Music in PECTus excavatum treatment (IMPECT) trial) to evaluate whether adjuvant recorded music interventions are indeed associated with less postoperative pain in children and adolescents undergoing the Nuss procedure for PE repair.

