### Interventions

Subjects in the intervention arm receive a recorded music intervention prior to and during surgery and postoperatively the first 3 days (see figure 1). The music intervention prior to surgery is 30 min long and takes place before the administration of premedication. After induction of general anaesthesia and after final positioning of the patient a headphone with music is applied and will remain during surgery. The headphones will be removed at the recovery unit, when patients are fully awake. The music interventions after surgery are each 30 min long and take place twice a day, in the morning and evening. In each hospital, the best times to start the intervention will be established to assure blinding of both the anaesthesiologists and pain specialists. Subjects in the control arm rest for 30 min prior to surgery and the administration of premedication, and wear a headphone without music during surgery. After surgery, they receive regular postoperative care without music interventions. Subjects in the control group are instructed to refrain from much listening to music during the hospital stay. The subjects in both control group and intervention group are requested to self-document all activities performed, such as listening to music, playing video games, using the computer and watching movies and television. Participation ends at the scheduled postoperative check-up at the outpatient clinic (see figure 1). All study measurements take place during hospitalisation and at the outpatient clinic. No extra visits to the hospital are required.

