### Anaesthetic treatment

There is no nationwide standard anaesthesia protocol for the Nuss procedure in the Netherlands. Therefore anaesthesia protocols differ between centres. Randomisation should control for such variation between centres. However, it will be analysed statistically.

All centres apply EMLA cream at the intravenous line insertion site. Furthermore, all patients receive epidural analgesia, which are preferably placed at fifth thoracic level. All centres used long-acting local anaesthetics with an adjuvant epidurally. General anaesthesia was induced and maintained by propofol combined with opioids and neuromuscular relaxation induced by rocuronium. Postoperative analgesia was maintained with a continuous epidural infusion of a long-acting local anaesthetic (ropivacaine 0.2% or bupivacaine 0.125%) with an adjuvant. All patients received weight-based doses of paracetamol and a non-steroidal anti-inflammatory drug postoperatively. After epidural removal pain was treated by oral opioids as required.

However, there are some major differences between hospitals: the Emma Children’s Hospital gives standard premedication with clonidine 150 μg and 300 mg gabapentin, while the other two hospitals do not give any pharmacological premedication. Furthermore, in Emma Children’s Hospital patients receive gabapentin 300 mg twice daily for 5 days and receive patient-controlled analgesia with morphine in addition to the epidural catheters. Finally, while Juliana and Sophia Children’s Hospitals use sufentanil 0.5 μg/mL as an epidural adjuvant, Emma Children’s Hospital uses clonidine 1 μg/mL.

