### Outcome parameters

The primary outcome parameter is pain, defined as the average pain score, as measured by a visual analogue scale (VAS-pain), that patients will report at the third day postoperatively. The scale of the VAS-pain varies from 0 to 100, whereas 0 is defined as no pain and 100 as the worst pain imaginable. This scale has been recommended and validated for the measurement of acute pain in children 8 years of age and above and is also sensitive to changes in pain levels postoperatively.^24–26^

Secondary outcome parameters include:

The morphine consumption in the first 3 days postoperative as calculated by the morphine equivalent daily dose/kilogram (MEDD/kg) and the consumption of other analgesics in milligrams.Physiological variables such as heart rate, blood pressure and respiratory rate will be measured throughout their hospital stay.Levels of anxiety and distress will be measured before surgery through the State-Trait Anxiety Inventory (STAI) for children. This questionnaire consists of two separate 20-item self-report rating scales for measuring trait and state anxiety. The trait anxiety is a relatively stable personality disposition, while state anxiety is the situation-related anxiety and this may differ depending on the stress of a particular moment.^27^ The questionnaire has been translated into Dutch and has been validated.^28^Quality of life will be measured before surgery and at their first check-up at the outpatient clinic through the Child Health Utility Questionnaire (CHU9D). This validated questionnaire consists of nine items that assess the child’s functioning across domains of worry, sadness, pain, tiredness, annoyance, schoolwork/homework, sleep, problems with daily routine and ability to join in activities.^29–31^Postoperative complications and length of hospital stay are recorded.The subject’s postprocedural pain after 3 months will be evaluated with the VAS, the CHU9D and the ‘TNO questionnaire for sport and physical activity’. This validated Dutch questionnaire assessed a person’s daily activities.^32^ This questionnaire serves to measure rehabilitation as a derivative of the postprocedural pain. Baseline measurements for the ‘TNO questionnaire for sport and physical activity’ will also be performed before surgery.Considering the potential influence of pain and the use of analgesics on length of stay, cost-effectiveness of the intervention will be determined through a cost-utility analysis.

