### Statistical analysis

The main study endpoint will be the VAS-pain score reported by the subject during the length of hospital stay, three times a day. The mean VAS-pain score of each day will be calculated per subject. The mean VAS-pain scores between the music and control group on the third day will be compared with an analysis of covariance (ANCOVA) test, with adjustment for the effects of centre and baseline VAS-pain score. The main analysis will be based on the intention-to-treat principle. In case of non-compliance, a sensitivity analysis will be performed using per-protocol analyses. A two-sided p value <0.05 will be considered to be statistically significant. For the primary outcome parameter, only the available data will be analysed (no imputation of missing data).

In a sensitivity analysis, we will also adjust for possible confounder variables in the linear regression model for the following variables: age, gender, body mass index and epidural use. Finally, we will also perform a second sensitivity analysis to determine if the effectiveness of the intervention depends on the type of music chosen, by adding these genres as categories to the linear regression model.

The VAS score of each time point will be analysed using a linear mixed model, with the baseline value (observed before surgery), group (control arm or intervention arm), centre and time point, and the interaction between group and time point as independent variables. Total consumption of analgesics and type of analgesics in milligrams will be added to the analyses. Also an interaction effect of centre and group will be examined due to variation in anaesthesia protocols in the participating centres. Using information criteria, it will be determined if it is necessary to add a random intercept and/or random slope of time point to this model, to account for the within-subject correlations. If required, a transformation of the outcome will be applied to ensure normality of the model residuals.

The secondary outcome parameters will be analysed as follows:

MEDD/kg and total dosage of other analgesia.

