There may be differences between centres in usage of patient-controlled analgesia and epidural anaesthesia. Therefore, the difference between the intervention group and the control group will be tested using multiple linear regression, with adjustment for the effects of centre. When necessary, an appropriate transformation of the outcome (MEDD/kg) or total dosage of other analgesia in milligrams will be performed to achieve a normal distribution of the residuals.

Score on STAI questionnaire and health-related quality of life (HRQoL).

The scores of the STAI and HRQoL questionnaires will be compared between groups using ANCOVA, with group, centre and the baseline STAI score and HRQoL score before the intervention or the resting period as independent variables.

Physiological measurements, including blood pressure, heart rate and respiratory rate.

These variables will be analysed using a linear mixed model, with the baseline value (observed before surgery), group (control arm or intervention arm), centre, time point, and the interaction between group and time point as independent variables.

Using information criteria, it will be determined if it is necessary to add to a random intercept and/or random slope of time point to this model, to account for the within-subject correlations. If necessary, a transformation of the outcome will be applied to ensure normality of the model residuals.

Complications, like postoperative ileus (number of days), nausea/vomiting (number of days and also antiemetics used) and pruritus.

The duration of postoperative ileus, nausea and vomiting will be compared between groups using a Mann-Whitney test, stratified by centre (ie, a Van Elteren test). The percentage of patients with pruritus will be compared between groups using a stratified χ^2^ test.

Length of hospital stay (number of days).

The length of hospital stay will be compared between groups using a Mann-Whitney test, stratified by centre (ie, a Van Elteren test).

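### The repeated-measures VAS model adjusts for analgesic consumption, a post-randomisation outcome, so its group terms do not estimate the randomised effect of music on pain

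*Protocol article*

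**What the plan says.** The Statistical analysis section of the protocol article sets out two analyses of VAS pain. The primary one is an ANCOVA of the day-3 mean, adjusted for centre and baseline VAS. The second uses every reading: "The VAS score of each time point will be analysed using a linear mixed model". Its independent variables are baseline value, group, centre, time point and group-by-time. Two additions follow. The first is "Total consumption of analgesics and type of analgesics in milligrams will be added to the analyses". The second is a centre-by-group interaction, motivated by the different anaesthesia protocols.

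Other sections describe analgesic consumption as follows:

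- **Outcome parameters** lists it as a secondary outcome: "The morphine consumption in the first 3 days postoperative as calculated by the morphine equivalent daily dose/kilogram (MEDD/kg"), together with other analgesics in milligrams.
- **Statistical analysis** compares it between arms: "the difference between the intervention group and the control group will be tested using multiple linear regression, with adjustment for the effects of centre".
- **Introduction** reports that in adult surgical patients "recorded music interventions reduce pain medication consumption and improve the management of pain and anxiety".
- **Interventions** says that the music arm will "receive a recorded music intervention prior to and during surgery and postoperatively the first 3 days", so postoperative doses come after both randomisation and the start of music.
- **Anaesthetic treatment** ties part of the dosing to pain: "After epidural removal pain was treated by oral opioids as required", and patients at one centre "receive patient-controlled analgesia with morphine in addition to the epidural catheters".

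**The concern.** A covariate that treatment can change is not a confounder of a randomised comparison. Here consumption may lie on the path from music to pain, and it is also partly a consequence of pain. Conditioning on it compares patients in the two arms who ended with equal analgesic intake, and randomisation does not protect that comparison.

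This mixed model is the only stated analysis that uses all the VAS readings taken three times a day over the stay. If its music effect is read from a consumption-adjusted fit, part of a real benefit may be removed, or a purely analgesic-sparing benefit may appear as more pain with music. The mixed model and the day-3 ANCOVA could then disagree only because they estimate different quantities.

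Labelling matters too. The preceding paragraph calls its adjustment for age, gender, body mass index and epidural use a sensitivity analysis. The consumption sentence carries no such label, and nothing says that the model without consumption will be reported beside it.

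**Working it through.** **The plan's own figure.** Inputs from Sample size: standardised effect 0.50, baseline correlation 0.3, power 90%, two-sided 0.05.

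n per arm = 2 × (1.960 + 1.282)² × (1 - 0.3²) / 0.50² = 2 × 10.51 × 0.91 / 0.25 = 76.5, so 77. This matches the protocol. The calculation belongs to the day-3 ANCOVA, which contains no analgesic term.

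**Effect of the adjustment.** Work in within-arm SD units. Let τ be the total (randomised) effect of music on VAS, δ its effect on consumption, and b the within-arm slope of VAS on consumption. In a linear model:

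adjusted effect = τ - b × δ

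Only τ = -0.50 has a source in the documents (the planning value). They give neither δ nor b, so δ = -0.4 and b = 0.3 to 0.5 are assumptions.

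- τ = -0.50, b = 0.3: -0.50 + 0.12 = -0.38 (24% smaller).
- τ = -0.50, b = 0.5: -0.50 + 0.20 = -0.30 (40% smaller).
- τ = 0, b = 0.3 and 0.5: +0.12 and +0.20, which is apparent harm.

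With these values the sign changes only if the size of τ is below b × 0.4, that is below 0.12 to 0.20. At the planning value it does not. The difference vanishes if δ = 0. It also vanishes in the degenerate case b = 0, where the covariate does nothing.

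**Repeated measures.** Simulated random-intercept models (77 per arm, 9 readings, 60 runs, b = 0.5) gave -0.51 without and -0.32 with consumption. Under a null VAS effect they gave +0.02 and +0.21. Both agree with the formula.

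**Direction.** A linear simulation (400,000 patients) varied how far consumption follows pain and how far the drugs lower VAS. Ranges are adjusted effects when music lowers consumption by 0.3 to 0.5 SD.

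| Assumed mechanism | Slope b | τ = -0.50 | τ = -0.20 | τ = 0 |
|---|---|---|---|---|
| Dosing follows pain, no drug effect on VAS | +0.49 | -0.35 to -0.26 | -0.05 to +0.04 | +0.15 to +0.24 |
| Dosing follows pain, drug effect -0.2 | +0.36 | -0.40 to -0.32 | -0.09 to -0.02 | +0.10 to +0.18 |
| Dosing follows pain, drug effect -0.3 | +0.12 | -0.47 to -0.44 | -0.17 to -0.14 | +0.04 to +0.06 |
| Dosing not driven by pain, drug effect -0.3 | -0.30 | -0.59 to -0.65 | -0.29 to -0.35 | -0.09 to -0.15 |

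With no effect of music on consumption, adjusted and unadjusted effects coincide in every row.

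**Power, as an indication only.** For a single measurement at 77 per arm, without baseline: 0.50 / √(2/77) = 0.50 / 0.161 = 3.10, power 0.87. With consumption, the residual SD is √(1 - b²) and the SE is inflated by 1/√(1 - 0.04/1.04). The SE is 0.157 at b = 0.3 and 0.142 at b = 0.5. The ratios are 0.38 / 0.157 = 2.42 and 0.30 / 0.142 = 2.11, so power is 0.68 and 0.56. Adding the stated 0.3 baseline correlation raises the unadjusted figure to 0.90. The trial was not sized on the mixed model, so these figures show scale and are not its actual power.

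**The case against.** **It touches no primary result.** This stands. The day-3 ANCOVA adjusts only for centre and baseline VAS, and the comparison of consumption is a separate analysis. A reader might infer that the main conclusion or the sample size is compromised; the documents do not support that.

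**The sentence may describe an extension, not a replacement.** The base model is complete before consumption is mentioned, and the centre-by-group term that follows also reads as an add-on. The text does not settle this, so one cannot say that the unadjusted model will go unreported. It remains an affirmative instruction without an exploratory label, and nothing says which fit carries the music effect.

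**It handles differences in analgesic regimen between centres.** Centre is already in the model, and the centre-by-group interaction is planned for that reason. The opposite overstatement, that analgesic type merely duplicates centre, also fails. Gabapentin, clonidine, patient-controlled morphine and epidural sufentanil follow centre, but paracetamol, an anti-inflammatory drug and as-required oral opioids are used at all three.

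**The size is assumed, and much dosing is fixed by protocol.** This stands. Continuous epidural infusion and weight-based drugs could make both δ and b small. The Introduction's reduction in consumption concerns adults, and the same section says that no definite conclusion exists for children and adolescents.

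**Consumption necessarily includes doses given after the reading being modelled.** A reader might infer this from the 3-day window, but that window defines MEDD/kg. The covariate in the mixed model is given in milligrams with no window. If its total spans the stay, early readings would be conditioned on later doses, but the text does not say so.

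**Reading pain in the light of analgesic use is a fair question.** This stands, as a labelled secondary question.

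**Conclusion.** The point holds for the repeated-measures VAS model only. With analgesic consumption and type included, its group and group-by-time terms do not estimate the randomised effect of music on pain. This follows from the protocol's own description of consumption as a postoperative outcome, compared between arms and partly driven by pain.

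The size is unknown. Under the assumed values, a total effect of -0.50 SD becomes -0.38 to -0.30, and a true zero becomes +0.12 to +0.20. It would be too strong to say that the adjustment must work against music. If relief from the drugs dominates, the effect grows, and if music leaves consumption unchanged there is no bias. A sign change needs a small total effect. That the direction cannot be known in advance is itself a reason not to rest the treatment comparison on this model.

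This should be fixed, but it is not critical, because the primary analysis and the separate analysis of consumption are sound.

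**What to change.** In the Statistical analysis section, state that the music effect on VAS over time comes from the mixed model with baseline VAS, group, centre, time point and group-by-time, without analgesic consumption or type. The section already uses this form for the physiological measurements. Keep the planned centre-by-group examination, and keep analgesic consumption as its own outcome with its centre-adjusted regression. If a consumption-adjusted VAS model is still wanted, report it beside the main one, labelled exploratory, with a note that it does not estimate the randomised effect.

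The cost is a change to one sentence, best made before results are known. It needs no new data or patients and leaves the 77 per arm (85 with dropout) unchanged. The only thing given up is that the consumption-adjusted result no longer carries the treatment comparison.

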### Economic evaluation

We will analyse the cost-effectiveness of the music intervention versus ‘standard care’ from a healthcare perspective, using the techniques of cost-effectiveness analysis and cost-utility analysis and following recommended methods for economic evaluations.^33^

Medical costs (ie, costs within the healthcare sector) will be analysed, including costs of surgeries, hospital days (on the ward or intensive care unit), medications (such as analgesics), diagnostic radiography and intercollegiate consultations. For the intervention group, costs of the music intervention will be added, mainly consisting of a Spotify subscription. In addition, costs of healthcare use after the initial hospitalisation will be calculated (eg, outpatient visits, consultations by telephone, (pain) medication and rehabilitation). Resource consumption for all these items will be derived from electronic databases at the participating centres and from a questionnaire (based on the iMTA Medical Consumption Questionnaire).^34^ Unit prices (calculated using economic cost prices or standard prices) will be multiplied by the quantities for each resource used, and then summed over the separate types of resource to give a total cost per patient. Non-medical costs (eg, out-of-pocket costs and costs of productivity losses incurred by the parents) will be ignored in this study, as these are expected to be relatively minor and not to differ notably between the study groups.

Regarding the patient outcomes, the economic evaluation will look at pain (as measured by the VAS) and HRQoL measured by the CHU9D. The CHU9D is a preference-based measure of HRQoL allowing for the calculation of quality-adjusted life-years (QALY), which is a commonly used health outcome measure to calculate the benefits of new interventions within cost-utility analyses for economic evaluation. QALYs will be calculated based on the CHU9D and using linear interpolation between measurement points.

Building on these data on costs and patient outcomes, incremental cost-effectiveness ratios will be calculated, expressed as incremental costs to obtain a reduction of one additional unit (10 mm or 1 cm) in the VAS score and as incremental costs per QALY gained. Otherwise, the economic evaluation will focus on dominance of one treatment over the other with respect to lower cost and greater effect. The time horizon of the analysis will be the 3 months’ follow-up period (starting at the beginning of the hospital admission for the PE repair). As a consequence, discounting will not be necessary. Analysis of uncertainty is illustrated through cost-effectiveness planes (via bootstrapping). Sensitivity analysis will be performed to assess the robustness of the analysis to certain assumptions.

